#### Statistical software

All analyses were performed with the R software (version 3.4.3, R Foundation for Statistical Computing, and Empower Stats, X&Y Solutions Inc., Boston, MA, USA).

### Safety and adverse events {22}

Adverse events pose potential risks during clinical treatment. In this study, all adverse events, encompassing significant adverse events, were meticulously documented in the CRF. This documentation included the time of occurrence, clinical manifestations, treatment process, duration, outcome, and association with the drug under investigation. For patients presenting abnormal laboratory test results, follow-up measures were carried out until the results reverted to normal or pre-trial levels or until it was ascertained that the abnormality was not related to the trial intervention.

### Frequency and plans for auditing trial conduct {23}

We currently do not have a specific audit plan outlined for this study. This decision is primarily influenced by the fact that data analysis is scheduled only at the conclusion of the study, and no interim adjustments are planned in the interim period. As such, we consider an interim audit unnecessary at this stage. However, we recognize the importance of monitoring and ensuring the integrity of the study processes and will duly consider incorporating an audit plan as the study progresses.

### Plans for communicating important protocol amendments to relevant parties {25}

Any amendments to the protocol and procedures must receive prior approval from the independent Ethics Committee of the Second People’s Hospital of Futian District through the amendment process. If granted approval, the modifications will be promptly communicated and documented in the online protocol registration.

### Who will take informed consent? {26a}

Upon initiating the trial, the principal investigator will elucidate the experimental procedures and obtain written informed consent, duly signed by each participant.

### Additional consent provisions for the collection and use of participant data and biological specimens {26b}

In the consent form, participants will be requested to grant permission for the utilization of their data in accordance with local privacy policies. In the event of withdrawal, participants will be asked to indicate their willingness to permit the utilization of acquired data. It is important to note that this trial does not involve the collection and storage of biological samples.

### Confidentiality {27}

To safeguard privacy, a unique alpha-numeric identifier will be assigned to each patient to anonymize personal information and contacts.

### Data management and monitoring {19}

In this study, a paper-based data collection methodology was employed for data management. Researchers transcribed the data from the original observation records of the subjects onto a CRF, which was subsequently signed by the principal investigator and promptly submitted to the clinical trial data custodian. Data entry and management were undertaken by team members uninvolved in the research intervention, utilizing an electronic database system for data input and validation. Regular meetings were held to analyze study data and monitor the project’s progress.

### Composition of the data monitoring committee, its role, and reporting structure {21a}

In this study, we currently have not established a Data Monitoring Committee (DMC). This decision is based on the nature and scale of the trial, as well as the availability of resources. Despite the absence of a DMC, we remain committed to ensuring the scientific and ethical integrity of the trial. We will implement alternative effective monitoring measures, including regular reviews of trial progress, monitoring safety data, and ensuring the quality and accuracy of the data. Additionally, we will maintain close collaboration with regulatory authorities and the ethics committee. We are dedicated to transparently reporting and sharing the progress and results of the trial.

### Interim analyses {21b}

Analyses in this study will be limited to regular monitoring of participant numbers conducted by the study management team and will not serve as a basis for study termination. The sole predetermined criterion for terminating the study is the occurrence of data protection incidents, particularly those posing a risk of expansion. The final decision regarding study termination rests with the primary sponsor.

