## Background {6a and 6b}

Gastrointestinal endoscopy is widely used for the diagnosis and treatment of digestive diseases. Midazolam and propofol are commonly utilized for procedural sedation during upper gastrointestinal endoscopy procedures [1]. Although both propofol and midazolam have demonstrated efficacy, they present specific limitations. Propofol provides desirable sedation depth and a short half-life (t1/2), enabling rapid patient recovery. However, it may cause respiratory depression, hypoxemia, and hypotension, necessitating continuous vital sign monitoring, including respiration. Midazolam, widely used, allows for easier sedation level titration compared to propofol, requiring less intensive monitoring. Its drawback is a half-life of 1–3 h [2, 3]. Remimazolam, a novel sedative and ester-based benzodiazepine, is rapidly hydrolyzed by liver esterase into its inactive carboxylic acid metabolite. With a shorter half-life than midazolam, remimazolam exhibits improved safety, facilitating swift awakening and early cognitive function restoration [4]. Phase III clinical trials of remimazolam for upper gastrointestinal endoscopy have demonstrated sedative effects and safety profiles in ASA grade (Appendix 1) I–II patients that are not inferior to propofol, with the sedative regimen outperforming propofol in certain aspects [5]. Procedural sedation safety and efficacy are primarily influenced by the patient’s physical condition. As ASA levels rise, the risk of adverse events during endoscopy increases [6]. Considering the requirements of upper gastrointestinal endoscopy, a safe and comfortable diagnostic and treatment experience during upper gastrointestinal endoscopy for these patients is important.

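### The stopping rule names data-protection incidents as the only predetermined ground for ending the trial, so the safety monitoring offered in place of a DMC has no predetermined consequence

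*Protocol article*

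**What the plan says.** Four statements in the protocol article bear on stopping the trial as a whole.

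- Interim analyses {21b}, on scope: "Analyses in this study will be limited to regular monitoring of participant numbers conducted by the study management team". The sentence goes on to say that these analyses "will not serve as a basis for study termination".
- Interim analyses {21b}, on grounds: "The sole predetermined criterion for terminating the study is the occurrence of data protection incidents".
- Interim analyses {21b}, on authority: "The final decision regarding study termination rests with the primary sponsor".
- Composition of the data monitoring committee {21a}: "we currently have not established a Data Monitoring Committee (DMC"). The substitute is a set of alternative measures, "including regular reviews of trial progress, monitoring safety data, and ensuring the quality and accuracy of the data", together with the undertaking that "we will maintain close collaboration with regulatory authorities and the ethics committee".

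Eligibility is restricted to ASA grade III or IV (Inclusion criteria {10}). The Background explains why this matters: "As ASA levels rise, the risk of adverse events during endoscopy increases". The Discussion adds that the safety of remimazolam for this procedure in high-risk patients has not been settled by earlier trials.

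**The concern.** A protocol article can reasonably leave stopping thresholds and reporting schedules to the full protocol. This one does something different: it states a closed list of predetermined grounds for termination, and the list has one item, which is not safety. A fuller document could add detail, but it could not add a predetermined safety ground without contradicting the word *sole*.

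The rule also fits badly with the safeguard described just before it. Section {21a} justifies having no DMC partly by promising that safety data will be monitored. Section {21b} then limits analyses during the trial to counting participants and gives safety no place among the grounds for stopping. If the monitoring showed, for example, a pattern of severe hypoxaemia or hypotension in one arm, the protocol would not say that anything follows for the trial.

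What is at stake is the protection of participants. The trial enrols patients chosen for their raised risk and is run because safety in them is uncertain.

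**Working it through.** The point concerns what the text provides, so the check is to set every section that touches stopping, monitoring or safety against one question: does it give a predetermined trial-level consequence of a safety concern?

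| Section of the protocol article | What it provides | Trial-level safety consequence? |
|---|---|---|
| Interim analyses {21b} | One predetermined ground (data protection); sponsor has the final say | No; safety is outside the list |
| Data monitoring committee {21a} | No DMC; safety data monitored; contact with regulators and the ethics committee | No ground, report or action named |
| Data management and monitoring {19} | Regular meetings at which study data are analysed | No action attached |
| Auditing {23} | Data analysed only at the end; no interim adjustments | No |
| Discontinuation or modification {11b} | Attending anesthesiologist may take an individual out for medical reasons | No; participant level only |
| Postoperative day 1 data collection | Telephone follow-up and recording of adverse events | No |
| Safety and adverse events {22} | Recording, attribution to drug, follow-up to resolution | No |
| Protocol amendments {25} | Prior ethics committee approval of changes | No |

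Two conclusions follow.

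1. **Grounds.** No section supplies a predetermined safety ground for ending the trial, and {21b} rules one out by calling its single criterion the only one. Suspension of enrolment, as distinct from termination, is not mentioned anywhere.
2. **Consistency.** The limit to participant numbers in {21b} does not agree with the monitoring of safety data in {21a} or with the analysis of study data at meetings in {19}. These sections suggest that more than counts will be looked at, so the limit cannot be meant literally. But neither says what a worrying finding would lead to.

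**Accrual, for context only.** Inputs are the planned 576 patients (Sample-size calculation {14}), and enrolment from 17 December 2022 with completion expected in October 2024 (Trial status {3}). Assume even accrual, and enrolment ending at about the completion date because follow-up is one day.

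- To 1 October 2024: 654 days / 30.44 = 21.5 months; 576 / 21.5 = 26.8 patients per month.
- To 31 October 2024: 684 days / 30.44 = 22.5 months; 576 / 22.5 = 25.6 patients per month.
- Per arm: 26.8 / 2 = 13.4 and 25.6 / 2 = 12.8 per month.

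This is the pace at which patients would enter while a concern awaited a decision. It does not measure the defect, because the document gives neither a serious-event rate nor a likely length of delay.

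**The case against.** The case on the other side is substantial, and much of it stands.

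- *The sponsor can stop the trial anyway.* This stands. *Sole* qualifies the predetermined criterion, not the power to stop, and the sponsor's final decision is not tied to listed grounds. A reader might infer that the protocol forbids stopping for safety; the text does not support that.
- *The clause denying a basis for termination covers participant counts only.* This stands. Its grammatical subject is the participant-number analyses. A reader might infer that it bars the safety review from leading to a stop, but it does not say so. The difficulty lies in the limit on analyses and in the word *sole*.
- *Harm would be seen at once.* Largely true. Sedation is given in a single session by an attending-level anesthetist with monitoring, the interventionists know the allocation, each event is attributed, and a patient can be taken out for medical reasons. Individual harms are unlikely to go unnoticed. A difference between the arms that builds up across patients is another matter, and that is what trial-level review is for.
- *Reporting lines, thresholds and review intervals belong in the full protocol.* This stands. Their absence from a journal article is no fault.
- *The sentence sits under an interim-analysis heading.* True, but it speaks of terminating the study without qualification.

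None of this supplies a predetermined safety ground, and none reconciles {21b} with {21a} and {19}.

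**Conclusion.** The point holds in a limited form. Section {21b} fixes a closed list of predetermined termination grounds that leaves out participant safety, and its limit on analyses conflicts with the safety monitoring in {21a} and the data-review meetings in {19}. A trial-level safety concern therefore has no predetermined consequence, although the sponsor may act ad hoc and individual harms are provided for.

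The size is modest. Nothing changes in the effect estimate, the error rates or the sample size, and how often a safety stop would be needed cannot be estimated from the document. The conclusion rests on reading *sole* in its ordinary sense and on no section outside those tabulated bearing on the matter. It does not imply that the trial needed a DMC: the plan may do without one, provided that the review it promises instead can lead to something.

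**What to change.** Amend Interim analyses {21b} in three respects:

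1. Delete *sole*, and name participant safety as a predetermined ground beside data-protection incidents.
2. State that the limit to participant numbers does not cover the safety review promised under {21a}.
3. State that a safety concern raised by that review pauses enrolment until the sponsor and the existing ethics committee decide whether to continue.

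Suggested text: *Apart from the safety review described under {21a}, analyses during the trial are confined to participant numbers, and those counts are not a basis for termination. The predetermined grounds for termination are participant safety and data-protection incidents. A safety concern raised by the review pauses enrolment until the sponsor and the ethics committee have decided whether the trial continues.*

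Clinical thresholds, the review interval and reporting lines for serious adverse events may stay in the full protocol. The amendment needs prior ethics committee approval under {25}. No new body is required, and the adverse-event data are already recorded under {22}. The costs are that a false alarm would briefly pause enrolment and that only patients enrolled after the amendment are protected.

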### Dissemination plans {31a}

The key components of our dissemination plan are outlined below: scientific journal publication, academic conferences, registration database, and patient and public communication, thereby fostering the widespread sharing of scientific knowledge and the advancement of best practices.

## Discussion

Upper gastrointestinal endoscopy is the gold standard for tumor diagnosis and treatment [8]. To provide a comfortable experience for patients and ensure their safety, medical institutions typically employ procedural sedation during upper gastrointestinal endoscopy [9]. Despite its benefits, procedural sedation presents several challenges, including timely airway emergency management, accurately controlling the depth of sedation, and managing respiratory and circulatory complications in high-risk patients [10, 11].

Procedural sedation is an anesthetic method that does not necessitate airway intervention and protection. It generally involves intravenous administration of sedatives and analgesics, with the level of sedation tailored to individual patients and endoscopic examinations or surgical procedures. Although no single drug can effectively achieve all targets, drug combination therapy is often the optimal approach for accomplishing the desired goals. Selecting appropriate sedative drugs based on their pharmacological properties is essential for ensuring safety and comfort in upper gastrointestinal endoscopic surgery [12]. Historically, benzodiazepines have been the drugs of choice for procedures sedation due to their anxiolytic and amnesic properties. Diazepam, lorazepam, and midazolam have been the primary benzodiazepines used for sedation. Midazolam, approved by the FDA since 1985 [13], remains the preferred benzodiazepine due to its rapid onset and superior amnesic effects compared to diazepam and lorazepam.

However, midazolam has significant interactions with other CYP3A4 inhibitors, such as cimetidine, erythromycin, diltiazem, verapamil, ketoconazole, and itraconazole, which can result in prolonged sedation time. Additionally, other benzodiazepine sedatives have half-lives ranging from 1.8 to 6.4 h, and their extended sedative effects may not be conducive to enhancing efficiency [2, 13].In conclusion, further research is needed to optimize drug selection and administration for procedures sedation during upper gastrointestinal endoscopy, with the aim of improving patient safety, comfort, and procedural efficiency [14].

In addition to midazolam, propofol is commonly used in procedural sedation methods due to its excellent sedative properties and short half-life. However, propofol is not without drawbacks, as it may cause aspiration pneumonia, cardiovascular and respiratory depression, hypoxia, and even necessitate tracheal intubation in some cases. Each sedative agent has its limitations for procedural sedation, and with the increasing demand for comfortable medical care, it is vital to enhance sedative quality during endoscopic examinations while ensuring safety. Developing new drugs is essential to addressing the safety and comfort concerns in procedures sedation [15, 16].

Remimazolam, a new sedative anesthetic, offers safety, comfort, and controllability advantages, presenting a new option for ideal procedures sedation. With no drug interactions with CYP3A4 inhibitors and superior pharmacokinetic and pharmacodynamic properties, such as a shorter elimination half-life, remimazolam is a promising agent for inducing and maintaining general anesthesia and sedation. It combines the characteristics of midazolam and remifentanil [17].

This study aims to compare the procedures sedative effect and safety of remimazolam with propofol in high-risk patients undergoing upper gastrointestinal endoscopy to evaluate remimazolam’s efficacy. Previous trials have predominantly included non-high-risk patients [5] or colonoscopy patients [18], making it unclear whether remimazolam provides a sedative effect and safety for upper gastrointestinal endoscopy in high-risk patients. The ASA level assessment is associated with an increased risk of adverse events or serious adverse events requiring unplanned intervention during endoscopic examinations and effectively predicts perioperative risk, serving as a valuable risk stratification tool [6]. This study seeks to apply remimazolam to procedures sedation in high-risk patients (ASA III and IV levels) undergoing upper gastrointestinal endoscopy to determine if it can provide a safe, comfortable diagnostic and treatment process and high-quality examination and surgical conditions.

This study has limitations, including the single-blind methodology, which may introduce performance bias. However, outcome evaluators and statisticians will be blinded, and efforts will be made to adjust for bias. Additionally, the study is limited to participants from a single center, and the results may only be applicable to the Chinese population. The trial’s short duration (1-day treatment) focuses solely on the short-term sedative effect and safety impact of remimazolam.

### Trial status {3}

This protocol is version 01. The participants enrollment commenced on 2022 December 17. The trial is currently in progress, with the anticipated completion date estimated to be in October 2024.

## Abbreviations

AEs: Adverse events
ARD: Absolute risk differences
BMI: Body mass index
CRF: Case report form
GAMM: Generalized additive mixed model
HR: Hazard ratios
ITT: Intention to treat
MOAA/S: Modified Observer’s Alertness/Sedation scale
NIBP: Noninvasive blood pressure
OR: Odds ratios
PP: Per protocol
SpO_2_: Pulse oxygen saturation.
